### Analysis

All analyses in CIC-PDD study will be performed based on an intention-to-treat statistical principle, adjusted for baseline characteristics [61]. Baseline, 6-month, and 12-month outcomes will be summarized by intervention arm and overall. The results will be presented as means (SD), medians (IQR), or numbers and proportions, as appropriate, with clustering taken into account.

Preliminary analysis will be conducted after the data have been cleaned to determine the pattern of missing baseline and follow-up data. We will conduct exploratory analyses to confirm expected distributions and assess the prevalence and patterns of missing data. Appropriate estimation techniques, such as multiple imputations, will be used to estimate missing data. Additionally, we will compare baseline characteristics between intervention and control group. The distribution of potential confounding factors will be taken into account as well as the participants who were able to complete baseline assessments and those who were unable to do so.

A multivariate regression model will be employed to estimate the effect of CIC-PDD on outcomes, accounting for potential confounding variables, including a random effect for CHCs and cluster size. Furthermore, we will explore the causal mechanism to gain a deeper understanding of how and why the results occur. Heterogeneity in treatment effects across sites and some baseline characteristics (e.g., sex, age, socioeconomic status) will be tested with interaction terms between these variables and the treatment status. To mitigate this effect of within-cluster correlation on estimator accuracy, we will cluster standard errors by CHCs. Moreover, sensitivity analysis will be carried out to check the robustness.

Additionally, we will conduct qualitative analysis to gain a better understanding of the implementation and policy processes, as well as to provide further insight into the results. All interviews and group discussions will be recorded and transcribed to capture the full information. Thematic analysis will be carried out on all qualitative data to identify themes. The theories outlined above will serve as the basis for developing interview topic guides and a coding framework.

Interim analyses and formal stopping rules are implemented to ensure the safety of participants and maintain integrity of the study results.

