### Study setting

The study sites are 8 CHCs from two counties of Weifang, Shandong, a province in eastern China. There are several reasons for choosing Weifang as our study settings. First, this is a priority city for several initiatives to strengthen primary care, including the integrated chronic diseases care approach and the establishment of single disease group management. Additionally, Weifang is a national pilot city for the construction of social psychosocial service system designated by China National Department of Health, making it feasible to conduct the interventions of both mental and physical conditions. Furthermore, both selected counties have tertiary hospitals, which can meet the need for a multidisciplinary team of specialists.

Recruitment of CHCs ran from July 2021 to November 2021.

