### Randomization and recruitment

#### Randomization

We randomized CHCs in each county on a 1:1 ratio, with an equal number of CHCs (*n* = 4) in each group. The allocation to the two arms was balanced based on size of the cluster, using the number of diabetic patients in each cluster.

Before implementation, allocation of clusters to each study arm was conducted by a statistician at the Peking University China Center for Health Development Studies. The statistician was not involved in implementation of the study.

To reduce the likelihood of bias caused by contamination and type II errors, cluster randomization was chosen. Patients within the clusters are allocated to the same group as their PCPs.

See Fig. 1 for an illustration of the randomization process.

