#### Sample size and power calculations

The study is powered to detect between-arm differences in achieving the primary outcome at 12 months post-randomization. Based on previous literature [47], a sample size of 480 patients (240 per group) at 8 CHCs offered greater than 80% power (*α* = 0.05; intraclass correlation coefficient 0.03) to detect a 20% absolute risk difference between groups on the primary outcome. To account for a potential 10–15% loss to follow-up (e.g., leave the area, die or refuse to take part in the study at follow-up) and to provide greater robustness against type II error, 280 cases were included in each of the two groups in the actual study. According to our previous systematic review [28], previous study sample sizes ranged from 58 to 417. Therefore, we expect that our study will have the largest sample size and, consequently, the highest efficiency and statistical power.

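### Standard errors are to be clustered on only 8 CHCs with no small-sample method named; in ordinary form the 5% test would reject too often

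*Protocol article*

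**What the plan says.** Under Study setting: "The study sites are 8 CHCs from two counties of Weifang". Under Randomization: "We randomized CHCs in each county on a 1:1 ratio, with an equal number of CHCs (*n* = 4) in each group". The same section states that "The allocation to the two arms was balanced based on size of the cluster, using the number of diabetic patients in each cluster".

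Under Analysis, the treatment effect comes from a regression model "accounting for potential confounding variables, including a random effect for CHCs and cluster size". Two sentences later, after the sentence on treatment-effect heterogeneity, comes the commitment: "To mitigate this effect of within-cluster correlation on estimator accuracy, we will cluster standard errors by CHCs".

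Under Sample size and power calculations, "a sample size of 480 patients (240 per group) at 8 CHCs offered greater than 80% power", with alpha 0.05 and an intraclass correlation of 0.03, for a 20-point absolute risk difference.

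The article does not say which reference distribution, degrees of freedom or finite-cluster adjustment goes with the clustered errors. It does not say that none will be used. Nor does it say whether the robust or the model-based standard error drives the primary test.

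**The concern.** The cluster-robust variance is justified as the number of clusters grows. With 4 CHCs per arm, the cluster residuals it is built from are shrunk towards zero by the fitted arm means, so the variance is biased downwards. It is also a noisy estimate, so a normal reference is too narrow. Cluster size, the covariate the plan names, varies only between CHCs. It uses one of the few between-cluster degrees of freedom and makes both problems worse.

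The stated purpose of the clustered errors is to deal with within-cluster correlation. In their default form, with this number of CHCs, they do so only in part. At stake are the coverage of the intervals and the false-positive rate for the two primary outcomes, SCL-20 and HbA1c, in a trial whose Discussion expects its results to feed into policy.

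**Working it through.** **Inputs.** From the article: G = 8 CHCs, 4 per arm; 480 patients for power (60 per CHC) and 560 enrolled (70 per CHC); alpha 0.05; ICC 0.03. Assumed: a two-sided test, normally distributed outcomes in the simulations, unequal CHC sizes of 40 to 115 where stated, and ICC varied from 0.01 to 0.05.

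**1. The plan's own figure.** The article states power above 80% and no actual type I error. Design effect = 1 + (60 - 1) × 0.03 = 2.77; effective n per arm = 240 / 2.77 = 86.6. The control rate is not given, so I varied it. At 0.20 against 0.40 the normal formula gives

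(0.20 × √86.6 - 1.96 × √(2 × 0.3 × 0.7)) / √(0.16 + 0.24) = (1.861 - 1.270) / 0.632 = 0.935, so power is about 82%.

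The same formula gives 91% at a control rate of 0.10, 79% at 0.25 and 75% at 0.40. The claim holds for control rates up to about 0.24 (or, by symmetry, from about 0.56), using a normal reference.

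**2. Exact type I error, equal clusters, treatment term only.** Let SS be the within-arm sum of squares of the 8 CHC means.

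- Uncorrected robust variance of the difference: SS/16.
- Unbiased variance on 6 df: (SS/6) × (1/4 + 1/4) = SS/12.
- Ratio: 12/16 = 6/8. The robust statistic is therefore a t on 6 df divided by √(6/8).
- Uncorrected, z: P(|t6| > 1.96 × √0.75 = 1.697) = 14.1%.
- With the factor G/(G-1) = 8/7 the ratio becomes 6/7. On z: P(|t6| > 1.815) = 12.0%.
- With that factor and t on 7 df: P(|t6| > 2.365 × √(6/7) = 2.189) = 7.1%.

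In this balanced case the rates do not depend on the ICC.

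**3. Unequal clusters and cluster-level covariates (null simulation).**

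| Setting | uncorrected, z | G/(G-1), z | uncorrected, t7 | G/(G-1), t7 |
|---|---|---|---|---|
| Treatment only, equal (exact) | 14.1% | 12.0% | 8.7% | 7.1% |
| Treatment only, unequal | 15.5% | 13.2% | 9.7% | 8.0% |
| Plus cluster size, balanced between arms, equal-information clusters | 18.2% | 15.9% | not run | 10.3% |
| Plus cluster size, unequal, size not balanced | 20.8% | 18.4% | 14.8% | 12.6% |
| Plus cluster size and county, unequal | 25.5% | 22.6% | 18.3% | 16.3% |

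The third row is closer to this trial's allocation, which balanced size between arms.

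**4. The random-effect reading.** Model-based REML errors with z gave 7.4% to 11.1% across the settings. ML errors with z gave 12.2% at ICC 0.03 with equal clusters, and 16.0% with cluster size in the model. A random-intercept model with sandwich errors on z gave 13-15% without cluster-level covariates and 21% with cluster size.

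**5. After correction.** A cluster-level analysis with t on the residual between-cluster df gave 4.6-5.1%. REML model-based errors on the same df gave 2.9-4.9%. CR2 errors on the same df gave 4.8-6.6%. Those residual df stand in for Kenward-Roger and Satterthwaite df, which were not simulated themselves.

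**6. Power with a t reference on 6 df, 480 patients.** Noncentral t gives about 81% at a control rate of 0.10, 69% at 0.20 and 61% at 0.40. On 5 df the figure at 0.20 is 66%.

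**The case against.** The article condenses a longer protocol that it says is available on request, and finite-cluster details often sit in an analysis plan. A reader might infer that the investigators have chosen to apply no correction. The text does not support that: it is silent. It is equally tempting to say that the intervals for both primary outcomes will be too narrow. That also goes too far, because a CHC random effect is named first, the clustered-error sentence follows the one on interactions, and nothing says which error gives the primary p-value.

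The size also depends on unstated settings. With G/(G-1), t on 7 df and no cluster-level covariate, the inflation is modest, at 7-8%. Balancing the allocation on cluster size pulls down the upper figures.

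All of this stands, and it makes the error rates conditional. It does not remove the point. The article does commit to a named estimator and a named cluster-level covariate, with 8 clusters. The lower figures require dropping that covariate or adding a method that the article does not name. Each z-based reading examined, robust or model-based, exceeded 5%.

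**Conclusion.** The concern holds in conditional form. Ordinary cluster-robust errors are unsuitable with 8 CHCs, and the plan needs a stated small-sample method.

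With a z reference the type I error is about 12-14% for the treatment term alone with equal clusters (13-16% with the assumed unequal sizes) and about 16-21% with cluster size. With G/(G-1) and t on 7 df it is about 7-8% and about 10-13% respectively. A random-intercept Wald z test gives about 7-12%: REML 7-11%, and ML about 12% at the plan's ICC without cluster-level covariates.

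The equal-cluster, treatment-only figures for robust errors are exact for normally distributed CHC means. The others rest on simulation with normal outcomes and an assumed distribution of cluster sizes. No single figure can be called the trial's actual error rate, because the article does not fix the reference distribution or the primary standard error.

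**What to change.** - **Primary inference:** state that the effect on each primary outcome is estimated from a REML mixed model with a random CHC effect, using the model-based standard error and Kenward-Roger degrees of freedom. If robust errors are preferred, specify the CR2 form with Satterthwaite degrees of freedom.
- **Name one primary standard error,** so that the random-effect and clustered-error sentences no longer compete.
- **Check:** report a cluster-level analysis of the 8 CHC summaries. Its residual df are 8 minus the number of cluster-level terms, counting the intercept: 6 with treatment only, 5 with cluster size, 4 with cluster size and county. A plain two-sample t test on 6 df would ignore the county and size structure of the randomisation.
- **Cluster-level covariates:** fix in advance which ones enter the model, since each costs one of these df.

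The cost is a change of analysis wording and the use of standard software. Intervals will be wider, and correctly so. Power will be below what the normal approximation suggests: about 69% instead of 82% at an assumed control rate of 0.20 on 6 df. The power statement should be restated on the reference distribution that is chosen.

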### Data management

Anonymity of participants will be protected through the removal of direct and indirect identifiers from the data during its analysis. We will retain data will for a period of at least 5 years after the project has been completed.

### The trial steering committee and data monitoring committee

The Trial Steering Committee (TSC) will be responsible for the independent supervision of the trial. Progress reports will be submitted by the research team to the TSC every 3 months. The TSC will closely monitor the study’s advancement and offer pertinent recommendations as needed.

Four external professionals who are not part of research team will serve as members of the data monitoring committee (DMC) for this trial. The committee will include a clinical trial expert, a biostatistician, a senior psychiatrist, and a senior diabetes specialist. The committee will be responsible for external oversight, monitoring the feasibility, data integrity, and safety of the study.

### Serious adverse events (SAEs) or adverse events (AEs)

Serious adverse events (SAEs) are not anticipated and we give a potential minor adverse events (AEs) list. The potential AEs that may occur during the course of the study include:Mild hypoglycemia without the need for medical intervention.Adverse effects of medications.Weight gain.Exacerbation of pre-existing conditions.Mild to moderate retinopathy.Common AEs in depression treatment include headache, dry mouth, insomnia, constipation, dizziness, fatigue, drowsiness, diarrhea, and sweating; most are mild to moderate in severity.

In the event of any SAES or AEs, regardless of their relation to the study intervention and irrespective of whether the intervention has been administered, immediate notification must be made within 24 h via telephone/fax to both the DMC and the principal investigator.

### Protocol amendments

When encountering deviations from the study protocol, the principal investigator will promptly report the situation. The method of timely reporting involves submitting a report to the Biomedical Ethics Committee of Peking University within 5 working days after the event occurs. Based on the feedback received, the principal investigator will assess and analyze the deviations from the study protocol, documenting this action in the progress report to identify potential trends that may indicate substantial issues. Furthermore, we will update the protocol in the clinical trial registry.

## Discussion

The CIC-PDD project aims to facilitate the development and innovation of PCIC model. Given the rising burden of NCDs, the high prevalence of concurrent diabetes and depression poses a significant and growing public health threat, especially in LMICs. Populations with diabetes and depression often struggle to adequate and reasonable care, despite the considerable illness and treatment burden that continues to increase. Worldwide, deficiencies in the availability, continuity, and quality of health services are considered key barriers to improving the health of this group, especially in LMCs. Urgent transformation of the health system into a PCIC system is needed. While CCM has been proven to be feasible and effective in some HICs, it remains unclear how integrated care models can be disseminated and implemented in routine care settings with limited resources, professional resistance, and competing priorities [28]. To our knowledge, CIC-PDD is the first study that is designed and carried out to explore effectiveness of CCM in China, and the first implementation study focused on patient with multimorbidity of physical and mental disorders. The results of CIC-PDD will contribute to the limited pool of knowledge about CCM and further the development and innovation of the concept and theory of integrated care globally. If the CIC-PDD project shows positive results, it will significantly improve future care for patients with multimorbidity in routine practice.

The CIC-PDD project will help to explore the potential of PHC in addressing mental health issues. A study found that only 0.5% of respondents with depressive disorders received adequate treatment in China, a number significantly lower in PHC context [62]. Treatment adequacy for major depressive disorder was merely 9.2%, even in specialist mental health services [32, 62]. The major reason behind this is the shortage of mental health resources, particularly in rural areas [63]. Therefore, there is an urgent need to close the treatment gap, especially for patients who have co-morbid chronic conditions. Empowering PCPs to deliver mental health services can help address the gaps in accessibility. However, studies have reported that PCPs are often inadequately trained, which hinders their ability to detect and manage common mental disorders effectively [62, 64]. Task-sharing has been recommended as a major strategy to address workforce shortages and close this gap, given the lack of mental health specialists in LMICs. Growing evidence shows that non-specialists can be trained to identify, diagnose, and treat patients suffering from mental health problems, leading to improved adherence and clinical outcomes [65–68]. Although the CIC-PDD project is designed for patients with diabetes and depression, we anticipate that the training of PCPs, the delivery of CC, and deployment of specialist teams will greatly enhance PCPs’ capacity to provide mental health service and improve access to and quality of mental health services for underserved population.

There will be several unintended and additional benefits derived from CIC-PDD, including (1) identification of unrecognized depressive symptoms among several thousand diabetic patients; (2) reducing PCPs’ stigma toward mental health disorders; and (3) facilitating the extension of mental and physical health services and the dissemination of advanced concepts (e.g., integrated care, CCM).

Additionally, it is anticipated that the CIC-PDD project has the potential to translate project results into policy. It will be the first RCT evaluating the real-world effectiveness of a task-shared collaborative team approach in China. Furthermore, by empowering and enhancing the skills of PCPs, the CIC-PDD project can lead to a lasting organizational change in the way patients with multimorbidity are managed in PHC. The study team has developed a stakeholder partnership with local health commission over the past decade, which will enable the results of CIC-PDD project to be translated into policy mandates and practice guidelines.

Inevitably, we anticipate that the implementation of the CIC-PDD project will face several challenges and limitations. One challenge is to provide PCPs with the necessary skills to deliver IC to patients in partnership with specialist team and health communicator, given that PCPs may have little mental health-related knowledge and are primarily engaged in clinical work. Another challenge is overcoming the complex interactions between mental and physical health system and establishing an efficient connection between the two.

The main limitation of this study is the fact that it is conducted in China, and the findings may not be immediately generalizable to other contexts of healthcare system. However, the CIC-PDD project aims to integrate interventions into existing healthcare delivery systems, which will provide insights into similar healthcare delivery structures in other regions.

### Trial status

The original version of the protocol (version 1.1 dated Sep 2, 2021) was approved by PU REB on October 12, 2021. Current version 1.2 (dated Sep 11, 2022) was approved by PU REB on October 11, 2022. The trial was registered on ClinicalTrials.gov on November 9, 2022. Recruitment commenced on December 1, 2022, and completed on January 20, 2023.

## Data Availability

The datasets utilized for analysis in the present study, along with the statistical code, can be obtained from the corresponding author upon reasonable request. Additionally, the complete protocol is also accessible upon request from the corresponding author.

## Abbreviations

LMICs: Low- and middle-income countries
T2DM: Type 2 diabetes
CCM: Collaborative care model
IC: Integrated care
PCIC: People-centered integrated care
PHC: Primary health care
NCDs: Non-communicable diseases
BPHSP: Basic public health service package
CIC-PDD: Community-based integrated care for patients with diabetes and depression
PCPs: Primary health providers
EUC: Enhanced usual care
RE-AIM: Reach Effectiveness Adoption Implementation Maintenance
CFIR: Consolidated Framework for Implementation Research
BCT: Behavior Change Theory
NPT: Normalization Process Theory
CM: Case manager
CHC: Community health center
BA: Behavioral Activation
CBT: Cognitive Behavioral Therapy
BSA: Bio-psychosocial Semi-structured Assessment
RCT: Randomized controlled trials
SCL-20: The Symptom Checklist-20
SF-12: The12-Item Short Form Health Survey
SDSCA: Summary of Diabetes Self-Care Activities Questionnaire
MTBQ: Multimorbidity Treatment Burden Questionnaire
MMAS: Morisky Medication Adherence Scale
PACIC: Patient Assessment of Chronic Illness Care
ORIC: Organizational Readiness for Implementing Change
LIM: Level of Integration Measure
PCCA: Patient-Centered Care Assessment Tool
ICER: Incremental cost-effectiveness ratio
QALYs: Quality-adjusted life years
CEAC: Cost-effectiveness acceptability curve
